### Retention

To address this critical issue, we will request the names, addresses and telephone numbers of three friends or relatives who would know how to get in touch with the participant. We request this information during the consent process and have found this approach helpful for retention in our other trials. We will implement additional strategies that have led to successful recruitment and retention of participants in clinical trials, such as: (1) making regular telephone contact to remind participants of upcoming study appointments and update their contact information, (2) providing a toll-free study telephone number to contact study staff and report a change of address or telephone number, (3) having an ethnically diverse staff from similar backgrounds as participants, and (4) providing a small stipend after study visits to compensate participants for their time and reimburse transportation costs [42-50].

The research team will stress the importance of compliance with the study sessions at enrollment. Participants will receive $30 to cover time and transportation for their baseline interview visit and $15 at each subsequent visit – the church screening for intervention participants, and the 6-month and 1-year follow-ups for participants in both groups ($75 intervention; $60 control). RAs will make reminder telephone calls to participants on the day prior to each interview session. Finally, RAs will be flexible in accommodating participants’ schedules, so they can be contacted evenings and/or weekends.

### Data and safety monitoring plan

To ensure the safety of participants and the validity and integrity of the data, a data and safety monitoring board (DSMB) has been established and meets approximately every 6 months. The DSMB includes senior investigators with expertise in stroke, hypertension and biostatistics. Adverse events will be reported to the appropriate IRBs and Privacy Boards.

### Study intervention

#### Intervention condition

It is widely accepted in the health promotion literature that interventions are more effective when they are culturally appropriate [51]. Thus, we optimize the potential impact of the intervention by enhancing its cultural appropriateness through cultural targeting. Using a transdisciplinary approach, we produced two culturally tailored, 12-min films (English and Spanish versions) in the first phase of the study. To accomplish this critical component, we organized a team of cultural leaders from local Black and Hispanic churches, a stroke expert, community-based researchers with expertise in culturally appropriate interventions, behavioral scientists – including narrative communication experts – a specialist in theory of knowledge acquisition, and a professional filmmaker. The director of the film is a seven-time Emmy award winning writer and producer of entertainment media who has experience in stroke narrative productions. To address the major barriers in the cascade of events and behavioral responses that occur in the pre-hospital setting of acute stroke, the screenplay has five didactic goals: (1) communicate knowledge of stroke symptoms, (2) communicate the *range of severity* with which the symptom may occur – for example, a slight slurring of the speech should be enough to precipitate action, (3) communicate the therapeutic benefit of calling 911, (4) overcome barriers to calling 911, including the reluctance to go to the ED, and (5) overcome issues related to denial or embarrassment if symptoms turn out not to be serious.

At baseline, the RA will provide participants with a study letter and the stoke film DVD (either in Spanish or in English) and ask them to watch it at least twice at home. The RA will also invite them to the church for one formal, assembly-style screening of the film. The RA will coordinate with the church champion to determine space and convenient schedules for the group film viewing. Participants will be reminded of the time and location of the film screening beforehand via phone. If a participant is unable to attend the larger group film screening, the RA will schedule an individual screening at a time and place more convenient for the participant.

### Viewing protocol

The number of exposures to the stroke films was selected based on theories governing “effective frequency” from marketing studies [52]. “Effective frequency” is defined as the number of exposures to an advertising message required for achieving effective communication and influencing consumer purchasing behavior. It is generally accepted that a single exposure, if relevant to the recipient’s concerns, may achieve effective communication. However, the marketing literature suggests that repeated exposure will be more effective and a minimum of three exposures may be required [52].

### Control condition

Educational brochures in English and Spanish are the most common form of stroke education. This practice occurs within inpatient, outpatient and community settings (particularly health fairs), and will represent “usual care” for the purpose of our study. The most common source of materials is from national organizations, such as the American Stroke Association (ASA), National Stroke Association (NSA) and National Institutes of Neurological Diseases and Stroke (NINDS). As such, an educational brochure will represent the control condition. For consistency, we will utilize one from the NINDS (in both English and Spanish) describing the five cardinal stroke symptoms and the importance of calling 911. The brochure will be distributed to control participants at the end of the baseline interview. There will be only one distribution of educational materials to the control group. Control participants will be asked to read over the brochure at least two times.

### Treatment fidelity

Assessment of fidelity will be based on the expanded Lichenstein treatment fidelity model developed by the OBSSR Behavior Change Consortium [53]. Similar to other DVD-based interventions [22,54], we will employ the following strategies to assess the dose of the intervention received by subjects: (1) all subjects will sign an attendance sheet to verify that they attended the DVD viewing in the church, (2) immediately following the in-church film screening, participants will complete the Stroke Action Test (STAT) measure, and (3) participants will also complete a Narrative Performance Scale (NPS). To minimize cross-contamination – some subjects may attend more than one church, or may know people from other participating churches – we will inform those exposed to the film not to divulge information about the film.

### Data collection and management

This study has a Research Core that is experienced in coordinating clinical trials and will be responsible for the following activities: (1) development of the computer-assisted data collection system, (2) staff training and certification in data collection, (3) randomization procedures, (4) data monitoring and quality control, (5) data processing, and (6) data analysis. The Research Core will prepare regular reports for internal and external monitoring of progress toward study milestones and provide blinded and unblinded data requests for DSMB meetings.

### Eligibility screening and baseline interview

The eligibility screening and baseline interview will be the same for both conditions. The RA will administer the eligibility screening and, if the participant is eligible, the baseline measure to all subjects via an electronic survey conducted on a laptop computer. This visit will be conducted at the church in a private location to ensure privacy. The eligibility screening will take approximately 30 min to complete, and the baseline screening will take approximately 45-60 min.

### Intervention film screening

After the in-church, assembly-style film screening, participants will complete the STAT and the NPS instruments. The STAT is a validated instrument that uses hypothetical scenarios to assess behavioral intent to call 911. The NPS is a validated instrument that assesses the extent to which participants are “transported” into the world of the narrative and became engaged with the story line and its characters [55].

### Follow-up interviews

Follow-up interviews will be the same for both conditions. The assessment will be administered in-person to study subjects using a structured interview format at 6 months and 1 year post-intervention. For the intervention group, 6 months will be measured from the date of the in-church screening. For the control group, 6 months will be measured from the date of the baseline interview. If after multiple attempts the RA is unable to schedule and complete the follow-up interview in-person, the participant will be given the option to complete the interview via telephone. If the staff is unable to reach a participant to complete the 6-month follow-up, the staff will still attempt to contact him/her for the 1-year follow-up.

### Church champion interviews

Following the initial year of formal data collection, annual interviews will be conducted with the church champion until year 5 of the study. This interview will assess the number of stroke film screenings conducted at the church after the formal 1-year study period.

### Study measures

#### Behavioral intent to call 911

The primary outcome will be self-reported behavioral intent to call 911 based on the validated STAT instrument [56]. This measure reliably predicts the actions that respondents would take if a stroke occurs and serves as our measure of stroke literacy. Most stroke knowledge assessments use either recall tasks (spontaneously naming stroke symptoms) or recognition tasks (selecting the correct stroke symptoms from a list), but the situation of acute stroke is different. During an acute stroke situation, symptoms are *experienced* or *observed.* The identification of symptoms is meaningless if it does not lead to urgent action. Knowing to call 911 when a stroke diagnosis is provided is not the same as calling 911 when stroke symptoms present.

The STAT measures behavioral intent to call 911 for suspected stroke symptoms using hypothetical stroke scenarios in which the stroke diagnosis is not provided. Each scenario features one of the cardinal stroke symptoms or a distracter symptom, and respondents are asked how they would respond to the scenario. The five cardinal signs of stroke include weakness, speech impairment, vision impairment, headache and dizziness [57]. The 21 scenarios are derived from these 5 cardinal “suddens” stroke symptoms. There are 21 because the 5 cardinal symptoms are presented in a variety of situations. All participants in the intervention and control conditions will be administered the STAT at baseline and the 6-month and 1-year follow-ups.

### Stroke knowledge

Following the STAT survey, we will directly assess knowledge of the five cardinal “suddens” stroke symptoms, which we will present in a multiple-choice format alongside seven distracter symptoms derived from the STAT. A composite score will be calculated by counting the number of correct responses to the five stroke symptoms [57] and seven distracter symptoms (maximum score = 12), modeled after the Behavioral Risk Factor Surveillance System (BRFSS) [58]. Participants will be administered the stroke knowledge battery at baseline and the 6-month and 1-year follow-ups.

### Demographics

At baseline, we will collect demographic information, such as age, sex, race, educational status and income. We also collect the following modules of the NINDS Common Data Elements (CDE) related to stroke: demographics, social status, medical history, family history, medication history and behavioral history. All time-varying demographic variables will also be collected at the 6-month and 1-year follow-up interviews (e.g., physical activity, diet, health, etc.).

### Sample size and power analysis

#### Power calculations for the primary outcome (behavioral intent to call 911 using the stroke action test)

Power calculations were based on both examination of endpoint differences and on rates of change over time using data from all three waves of data collection. The main calculation shown in Table 1 is for the primary analysis examining rate of change. The outcome is treated continuously, and we assumed a two-tailed test with α = 0.05 and 1-β = 0.80. The following assumptions, based on the literature on stroke literacy and stroke action using the STAT [56], were used to calculate sample size and power: R =0.85 (reliability); g = 2 (group); σ = 17.83 (pooled SD of examinee subgroups); δ = 8, 9, 10 (Stroke Action point reduction); d = δ/σ where δ is the endpoint mean differences, and d is Cohen’s d (0.45, 0.50, 0.56). The number of churches posited to be economically feasible is 7 per arm, and the cluster size is 18, with over-recruitment to 25. The ICC derived from data from over 30 churches participating in a separate, ongoing randomized trial of a church-based intervention was posited to be 0.02. Thus, the VIF = 1+ (clustersize-1)*ICC = 1.34. It was assumed that ρ = 0.6 (the average correlation between baseline and follow-up).

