**Table 1 Tab1:** **Sample size (**
***n***
**per group) for different effect sizes with power >80%**

	**δ = 8 (d = 0.45)**	**δ = 9 (d = 0.50)**	**δ = 10 (d = 0.56)**
ρ = 0.6	79	62	50
ρ = 0.6	δ = 8.19 (d = 0.47)	δ = 7.10 (d = 0.40)	δ = 6.34 (d = 0.36)
	75	100	125

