### Power for rate of change on the stroke action test

Using formulas based on Diggle et al. [59], assuming three time points (baseline, 6 months and 1 year), the requisite sample sizes are shown in Table 1. It was determined, based on both sets of calculations, that 125 subjects per group will provide >80% power to detect an 8-point change in STAT. Lower effect sizes, about 6 points, can also be detected based on testing the Time X Group interaction in a mixed model, which allows for heterogeneous variances, clustering, unreliability and serial correlations.

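### Table 1 is presented as three-wave rate-of-change power but reproduces from a single-follow-up baseline-adjusted formula; on the stated inputs the slope test detects about 7.1 points at 125 per group, not about 6

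*Protocol article*

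**What the plan says.** The section on power for the primary outcome says that both endpoint differences and rates of change were considered, and then: "The main calculation shown in Table 1 is for the primary analysis examining rate of change". The next section, on power for rate of change, attributes the table to longitudinal formulas: "assuming three time points (baseline, 6 months and 1 year), the requisite sample sizes are shown in Table 1". It concludes that 125 per group gives more than 80% power for an 8-point change, and adds: "Lower effect sizes, about 6 points, can also be detected based on testing the Time X Group interaction in a mixed model".

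The data analytic plan makes the Group × Time F-test the primary test. It also says that no covariates are proposed for the main analyses of treatment effects. Baseline is explicitly included in the model only for the binary knowledge outcome.

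The same power section, however, defines δ as a difference in endpoint means and ρ as the average correlation between baseline and follow-up. Those are the ingredients of a single-endpoint calculation.

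**The concern.** A three-wave slope and a baseline-adjusted single endpoint have different variances. If the table's numbers belong to the second, the printed sample sizes and detectable differences are not those of the test named as primary. At stake are the first row of Table 1, which would be about 20% too small for a slope test (79 against 99), and the 6-point statement, which refers specifically to the interaction test. The total of 125 per group is justified by the 8-point claim, so that claim has to be checked separately.

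**Working it through.** **Inputs, all from the power section.** Two-sided α = 0.05 and power 0.80, so (1.960 + 0.842)² = 7.849; σ = 17.83; δ = 8, 9, 10; ρ = 0.6; R = 0.85; VIF = 1 + 17 × 0.02 = 1.34.

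**Step 1: reproduce Table 1.** Single follow-up, baseline-adjusted: n per group = 2 × 7.849 × (1 − ρ²) × VIF / (R d²), with d = δ/σ.

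- Constant: 2 × 7.849 × 0.64 × 1.34 / 0.85 = 15.84.
- d = 8/17.83, 9/17.83, 10/17.83 = 0.449, 0.505, 0.561.
- n = 78.7, 62.2, 50.4 (printed 79, 62, 50).
- Detectable δ = 17.83 × √(15.84/n) at n = 75, 100, 125: 8.19, 7.10, 6.35 (printed 8.19, 7.10, 6.34).

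All six entries match to rounding, so both rows come from this one formula. A search over slope, change-score and time-averaged variance factors, with several treatments of VIF and R, found no other combination that matched all six. Some came close on the first row alone, because 0.64 × 1.34 / 0.85 = 1.009 leaves the sizes almost equal to an unadjusted two-sample calculation (78, 62, 50). They miss the printed detectable differences or need inputs other than those stated.

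**Step 2: the calculation Table 1 is said to be.** Slope over waves at 0, 0.5 and 1 year, equal correlation between waves, δ the one-year difference. The sum of squared time deviations is 0.5, so the variance factor is (1 − ρ)/0.5 = 2(1 − ρ) = 0.80.

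- Constant: 2 × 7.849 × 0.80 × 1.34 / 0.85 = 19.80.

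| | 8 | 9 | 10 points |
|---|---|---|---|
| n per group, printed | 79 | 62 | 50 |
| n per group, slope | 98.3 → 99 | 77.7 → 78 | 62.9 → 63 |

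| | 75 | 100 | 125 per group |
|---|---|---|---|
| Detectable δ, printed | 8.19 | 7.10 | 6.34 |
| Detectable δ, slope | 9.16 | 7.93 | 7.10 |

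The slope needs 0.80/0.64 = 1.25 times as many participants. The 7.10 printed for 100 per group is therefore the slope figure for 125.

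**Step 3: power of the slope test at 125 per group.** SE = 17.83 × √(2 × 0.80 × 1.34 / (0.85 × 125)) = 2.533.

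- 6 points: 6/2.533 − 1.960 = 0.41, power about 66%.
- 8 points: 8/2.533 − 1.960 = 1.20, power about 88%.

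Under Table 1's own formula the SE is 2.265, and power for exactly 6 points is about 75%.

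**Step 4: how far the answer depends on modelling (125 per group, 80% power).**

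| Assumption | Detectable points |
|---|---|
| Slope, church effects constant over time (no VIF), R kept | 6.13 |
| Slope with a common baseline mean in both arms (factor 0.629), VIF and R kept | 6.29 |
| Slope, VIF and R as stated | 7.10 |
| As stated, but t with 12 df (14 churches − 2) | 7.7 |
| Single-endpoint formula of Table 1 with 12 df | 6.9 |
| Time categorical, 2-df test, full effect from 6 months | 6.81 |
| Time categorical, 2-df test, linear divergence | 7.86 |
| Slope, correlation decaying with time (0.7/0.5, or 0.6/0.36) | 7.9 to 9.0 |

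With 12 df, slope power is about 59% for 6 points and 83% for 8 points.

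**The case against.** The strongest reply is that 7.1 is one modelling choice among several. The VIF of 1.34 is a cross-sectional inflation. Church effects that are constant over time cancel from a slope, and the article gives no church-by-time correlation. Without that inflation the slope detects 6.13 points. A Group × Time model can also recover baseline-adjusted precision: if both arms share a baseline mean, as randomisation justifies, the variance factor is 0.629 and the detectable difference is 6.29, close to Table 1. Dropping the second allowance for reliability, on the assumption that 17.83 is an observed-score SD already containing measurement error, gives 6.54 with the VIF and 5.65 without it.

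This stands in part. It rules out saying that the design cannot detect about 6 points, or that a Group × Time test necessarily lacks the precision of baseline adjustment. It does not rescue the text. The article applies both VIF and R, describes a model with a treatment-group term and states no common-baseline constraint. How baseline enters may be settled in an analysis plan that is not shown, but the printed numbers would still not come from the three-wave formula named as their source. Decaying correlation also moves the detectable difference the other way.

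Three further inferences are tempting and should not be drawn:

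- **That the trial is too small.** The 8-point claim holds at about 88%, or 83% with 12 df.
- **That a null result will be read as excluding 6 points.** The plan commits to a 95% confidence interval, and that interval is what would show which effects are excluded.
- **That printing 6.34 and writing about 6 is itself a contradiction.** It is loose rounding. Likewise, the printed "δ = 8.19 (d = 0.47") should read 0.46, since 8.19/17.83 = 0.459. That is clerical.

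**Conclusion.** The mismatch is real. Table 1 is labelled as three-wave rate-of-change power, and its entries are single-follow-up baseline-adjusted power. On the stated σ, ρ, VIF and R, with equal correlation between waves, the slope test needs about 25% more participants than the first row shows. It detects 7.10 points at 125 per group rather than 6.34 and has about 66% power for 6 points. The statement that the interaction test can detect about 6 points is therefore unsupported on the article's own inputs. It becomes defensible only under assumptions that the article does not state, such as church effects that cancel from the slope or a common baseline mean. The 12-df figures also rest on an assumption the article does not state, so they belong in a sensitivity range. The sample size and the 8-point claim are unaffected. This should be fixed.

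**What to change.** Choose one test and make the table, its label and the model agree:

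- **(a)** Relabel Table 1 as baseline-adjusted single-endpoint power and make the primary model baseline-adjusted to match. One way is a three-wave model with a common baseline mean across arms, which detects about 6.3 points at 125 per group.
- **(b)** Keep the Group × Time slope as it stands. Recompute Table 1 as 99, 78 and 63 per group and 9.16, 7.93 and 7.10 points, and replace the 6-point statement with about 7.1.

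In either case, report the range and name the assumption behind each figure: about 6.1 if church effects cancel from the slope, 7.1 with the full VIF, and 7.7 with the full VIF and 12 df (6.9 for the single-endpoint formula with 12 df). Correct d for 8.19 to 0.46 in passing.

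The cost is restated figures, one sentence on how baseline enters the model and, under (b), a slightly less favourable detectable effect. No participants or churches need be added.

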**Table 1 Tab1:** **Sample size (**
***n***
**per group) for different effect sizes with power >80%**

	**δ = 8 (d = 0.45)**	**δ = 9 (d = 0.50)**	**δ = 10 (d = 0.56)**
ρ = 0.6	79	62	50
ρ = 0.6	δ = 8.19 (d = 0.47)	δ = 7.10 (d = 0.40)	δ = 6.34 (d = 0.36)
	75	100	125

### Power for rate of change on the stroke action test

Using formulas based on Diggle et al. [59], assuming three time points (baseline, 6 months and 1 year), the requisite sample sizes are shown in Table 1. It was determined, based on both sets of calculations, that 125 subjects per group will provide >80% power to detect an 8-point change in STAT. Lower effect sizes, about 6 points, can also be detected based on testing the Time X Group interaction in a mixed model, which allows for heterogeneous variances, clustering, unreliability and serial correlations.

### Power calculation for the secondary outcome (stroke symptom knowledge)

For this binary outcome, it is posited that the control group will improve by 6%, starting at 4% with knowledge, based on a composite score for correct answers to the five cardinal “suddens” symptoms [57]. Given randomization, the intervention group is posited to start at the same level and improve 24%, for a net improvement of 18%. The assumptions are: R =0.85 (reliability); g = 2 (group); cluster size = 18; ICC = 0.02; VIF = 1+ (clustersize-1)*ICC = 1.34. A sample size of 125 subjects per group will provide 80% power to detect a group difference in the rate of increased knowledge at 6 months, from a baseline rate of 4% to a desired level of 28%.

